## 5. Study Procedures

---

### 5.1 Visit schedule overview

The patient-related activities of the GLUMIT-DG study can be divided into 3 phases:

- **Screening Phase:** Screening to determine eligibility and receive training on the use of an iPro which is a CGM used for retrospective analysis of CGM results. While wearing the device the subject is blinded to their sensor glucose values. This period is so that the subjects can demonstrate a willingness to wear a sensor, gain proficiency in inserting a sensor, and provide the study baseline data of their CGM readings (retrospectively). This will occur over 2-8 weeks and include 2 visits for gastric related testing as well as iPro training. To progress in the study the subject will need to have at least 216 hours of iPro readings.
- **Run-in Phase:** Initiation of insulin pump training and training in the use of real-time CGM (4 visits over a minimum of 2 weeks up to a maximum of 8 weeks)
- **Follow-up Phase:** Study treatment to assess the safety of using RT-CGM as an adjunct to SMBG-guided insulin pump therapy over 24 weeks (6 visits)

The visit and data collection schedule described below in detail is summarized in Appendix 10.2

### 5.2 Screening and baseline data collection overview

Many of the GLUMIT-DG participants will come from the Gastroparesis Registry or from the patient rosters of the study physicians. Patients who appear to be eligible after chart review and completion of standard of care tests and procedures for gastroparesis will be invited to undergo screening for the GLUMIT-DG study. Patients considered by the clinical center study physician as likely to be eligible for participation in the GLUMIT-DG study may be consented, registered, and screened at a visit that is part of the ongoing clinical care of the patient. Screening tests should be completed according to the standard of care as outlined in the Standard Operating Procedures IV: Standard of Care for Patients with Diabetic Gastroparesis.

Recording of screening data on study forms may not start until the patient has signed the GLUMIT-DG consent statement. Screening and baseline data collection procedures will include review of the patient's medical chart and completion of questionnaires, physical examination, hemoglobin A1c testing, monitoring of blood glucose values, and study specific clinical procedures on patients. Data abstracted from a patient's chart may include laboratory, endoscopy, radiology, and gastric emptying scintigraphy test results. Prior therapy for gastroparesis and diabetes will also be reviewed.

All participants who sign the consent statement will be registered in the GLUMIT-DG study. Each participant who is registered in the GLUMIT-DG study and who starts screening will be accounted for at the end of the screening phase, as either a screening success (enrollment) or a screening failure. A screening failure is defined as a participant who signed the consent form and was registered in the GLUMIT-DG study, but is found to be ineligible prior to enrollment. Screening failures include patients who meet medical eligibility criteria but failed the RT-CGMS training or changed their mind and do not consent to enrollment into the study after careful consideration of the study demands on their personal time. The reason for screening failure will be recorded on the GLUMIT-DG enrollment form and keyed in the study database.

Screening and baseline data collection procedures will be conducted over three clinic visits. The goal of the first screening visit is to obtain consent, register the prospective participant for GLUMIT-DG, start recording screening data regarding the study inclusion and exclusion criteria on case report forms, and initiate iPro training; the goal of the second and third screening visits is to complete collection of baseline data including EGG and satiety tests on patients who appear to be eligible and complete iPro training. This separation of procedures between two study visits is somewhat arbitrary and is provided as a

guideline. Study screening procedures and data collection can be organized as appropriate at each clinical center. The procedures completed during the screening phase include:

**Gastric emptying scintigraphy:** Patients who have not had a standardized 4 hour gastric emptying scintigraphy within 1 year of registration or whose previous gastric emptying scintigraphy is of inadequate quality must have a standard of care gastric emptying scintigraphy as part of screening prior to enrollment. Instructions for the gastric emptying scintigraphy are found in the GLUMIT-DG Standard Operating Procedures I: Clinical Center Operations.

**Upper endoscopy:** Patients who have not had an upper endoscopy within 1 year of registration must have a standard of care upper endoscopy as part of screening prior to enrollment to rule out other potential causes of symptoms such as mechanical obstruction, inflammatory or other structural lesions of the GI tract, or non-gastrointestinal causes

### 5.3 Screening visits and iPro training

**Screening visit 1:** The patient should be in a fasting state (no food or drink except up to 120 mL (4 oz) of water after midnight the night before) for this visit. The patient will sign the GLUMIT-DG consent at or prior to screening visit 1 and will undergo a history and physical examination to identify other illness and contraindications for participation. In addition, blood will be drawn to measure their hemoglobin A1c level. A patient's hemoglobin A1c level must be 8.0% or higher in order to be eligible for this study. Laboratory test results that need to be recorded from chart review or obtained as part of screening include: complete blood count (CBC): white blood cells, red blood cells, hemoglobin, and platelets; a comprehensive metabolic panel: sodium, potassium, chloride, carbon dioxide, calcium, glucose, blood urea nitrogen (BUN), creatinine, albumin, total protein, alanine aminotransferase (ALT), aspartate aminotransferase (AST), and bilirubin; and thyroid stimulating hormone (TSH). The Patient Assessment of Upper Gastrointestinal Disorders - Quality of Life (PAGI-QOL) and the Patient Assessment of Upper Gastrointestinal Disorders - Symptom Severity Index (PAGI-SYM) questionnaires will also be completed as well as the Baseline Medical History and Physical Examination forms.

**iPro training:** At a clinic visit as early as possible during the screening phase, patients will be seen by a diabetes educator to undergo training on measuring their interstitial glucose levels using the iPro. The iPro involves wearing a sensor device, which has a needle that is inserted in the subcutaneous tissue to continuously measure blood glucose levels. The sensor is calibrated according to blood glucose results taken from finger sticks. This is a device that collects interstitial glucose readings, but the readings are not displayed to the patient, so no insulin dose decisions are made based on CGM readings. Patients will measure their blood glucose levels using a standard finger stick method and will be required to do so 4 times daily using a glucose meter. During this period, patients will continue to take their regular diabetes medications or insulin treatment including those who already wear an insulin pump. This iPro data will not be used for adjustment of diabetes therapy since the patient cannot see the data.

**Screening visit 2:** Patients should consult with their GLUMIT-DG certified endocrinologist 24 hours prior to visit and return to the clinical center in a fasting state (no food or drink except up to 120 mL (4 oz) of water after midnight the night before) on a separate day after the first screening visit to continue with study procedures and baseline data collection for electrogastrograms with non-caloric and caloric satiety tests (EGG), electrocardiogram (ECG), and autonomic function testing. If patients normally take insulin, they will be asked to take only their normal BASAL insulin and hold meal insulin, using supplements of insulin to correct high glucose AS PER their doctor's instructions. If patients are using a pump, they will be requested to keep their usual basal rate and hold meal boluses and to use supplemental insulin if their home glucose meter indicates a high glucose by using the bolus calculator of their insulin infusion pump or as suggested by their doctor's instructions. Upon arrival to the clinic, patients will have

10 mL of blood drawn for plasma banking to measure inflammatory and immune markers or plasma proteins to ascertain the effects of controlling blood glucose during the GLUMIT-DG study. Patients will have their blood glucose level measured using a finger stick method to ensure their blood glucose is less than 270 mg/dL. If the blood glucose level is higher, then a blood sample will be taken and sent to the lab for confirmation and supplemental insulin will be ordered by the endocrinologist or diabetes educator of the research team to decrease the blood glucose to less than 270 mg/dl. Once confirmation is made that the patient's blood glucose level is less than 270 mg/dL, the electrogastrograms with non-caloric and caloric satiety tests will be performed.

**Electrogastrogram (EGG) with satiety testing:** Patients should consult with their GLUMIT-DG certified endocrinologist 24 hours prior to making any adjustments to their insulin for EGG with satiety testing. They may take their normal morning medications with a small amount of water (up to 120 mL) up to two hours prior to the EGG with satiety testing, but should refrain from coffee, juice, or tea. EGG is the recording of the myoelectrical activity of the stomach using electrodes similar to an electrocardiogram. EGG electrodes are placed on the abdominal skin. Skin preparation for these electrodes will consist of cleaning the skin with an electrode paste and then applying a conduction gel which is then wiped off. If needed, the abdominal skin where electrodes will be positioned is shaved. If both the caloric EGG and non-caloric EGG tests are performed on the same day, then the caloric should be performed approximately two hours after completion of the non-caloric water load test.

Staff should thoroughly review both the finger stick blood glucose and CGM data within 24 hours prior to performing either the caloric satiety test using Ensure® or non-caloric satiety test using water. Patients must meet the following criteria in order to undergo EGG with satiety testing:

- Glucose levels between 100 – 270mg/dL measured by finger stick immediately prior to testing and,
- No indication of severe hypoglycemia (glucose <50mg/dL) or hyperglycemia (glucose >500mg/dL) within the 48 hours prior testing

Patients that do not meet these criteria will be managed at the discretion of the GLUMIT-DG gastroenterologist and endocrinologist. The EGG test must be postponed for another day when it can be safely performed and when the patient's symptoms and glucose reading are within allowed range. Staff should not attempt to manage the patient solely for the purpose of completing the EGG test on the same day. If after two attempts, the patient still does not meet the safety criteria, then the test should not be performed.

**Non-caloric satiety testing:** For the non-caloric water load satiety test, patients will undergo a 15 minute fasting baseline EGG recording and a 30 minute post-water load EGG recording. After completion of the baseline period, patients will drink bottled spring water refrigerated at 4 degrees C) for a 5 minute period until they feel completely full. Patients will drink from an opaque 150 mL cup which will be filled out of sight so that the volume consumed is not readily apparent to minimize the potential of introducing bias. In addition, no information regarding the total volume of water ingested will be communicated to the patient. The total volume of water ingested will be recorded on the EGG and Water Load Satiety Test form. Symptoms of nausea, bloating, abdominal discomfort, hunger, and stomach fullness will be recorded on a visual analog scale at baseline and at 10, 20, and 30 minutes after ingestion of the cool water. The EGG will be recorded and analyzed for the 15 minute fasting baseline and post water-load period at 0-10, 11-20 and 21-30 minutes after ingestion of the water load.

**Caloric satiety testing:** Approximately two hours after completion of the non-caloric water load test with EGG recording, patients will undergo a caloric satiety test. Patients will undergo a 15 minute baseline fasting and 60 minute post-nutrient EGG recording. After completion of the baseline period,

patients will drink a cup (150 mL) of refrigerated (at 4 degrees C) Ensure® (1.1 kcal/mL) at a rate of 150 mL every 5 minutes until they feel completely full. Patients will drink from an opaque cup which will be filled out of sight so that the volume consumed is not readily apparent to minimize the potential of introducing an assessment bias. In addition, no information regarding the total volume of Ensure® ingested will be communicated to the patient. The total volume of Ensure® ingested will be recorded on the EGG and Satiety Test form. The satiety test will be analyzed by the total amount of Ensure® consumed. Symptoms of nausea, bloating, abdominal discomfort, hunger, and stomach fullness will be recorded on a visual analog scale at baseline and at 10, 20, 30, and 60 minutes after ingestion of Ensure®. The electrodes will then be removed. The EGG will be analyzed for the fasting and post nutrient load periods corresponding to symptom assessments at 0-10, 11-20, 21-30, 31-40, 41-50 and 51-60 minute intervals. The percentage distribution of the power in the normal frequency range (2.5-3.75 cycles per minute [cpm]), tachygastria (>3.75-10 cpm), bradygastria (<2.5 cpm) and duodenal-respiration (>10 cpm) will be calculated. A power ratio comparing mean signal amplitudes between postprandial and preprandial power will be calculated. The dominant frequency, and the percentage of time in the dominant frequency will be calculated and recorded.

Patients will receive 1 unit of insulin for every 15 grams of Ensure® consumed during the caloric satiety testing to reduce the likelihood of severe postprandial hyperglycemia. Patients blood glucose levels will be closely monitored using their home glucose meter. Patients will be monitored for 2 hours after beginning the Ensure® satiety testing to assure their blood glucose level does not exceed 300 mg/dL. If a patient's blood glucose level exceeds 300 mg/dL, additional insulin will be given to bring it down to 250 mg/dL as per the suggestion of the endocrinologist or diabetes educator of the team.

**Autonomic function with ECG:** Patients will have a baseline ECG followed by an ECG tracing for heart rate variability. Patients will be asked to remain in the supine position while breathing slowly for a five minute period. From this ECG tracing, vagal cholinergic function will be estimated by quantifying changes in heart rate during inspiration and respiration. R-R interval will be analyzed for mid and high frequency fluctuations (max to min ratio normal is 30:150).

At the conclusion of the ECG, patients will be seen again by the diabetes educator to continue with their iPro training. If further training is needed, per the judgment of the diabetes educator or the diabetologist, extra visits or phone calls may be scheduled. Once the training is completed (as per the diabetes educator or the diabetologist), the patient will be requested to use the iPro for a period of 2 weeks and perform 4 finger sticks per day which will be used for calibration of the iPro. If 216 hours of good iPro data is obtained during the 2-week period, training will be considered successful and the patient will proceed with the run-in period. Alternatively, if a patient has not demonstrated adherence with checking blood glucose levels using the glucose meter 4 times daily or if the iPro data do not fulfill the criteria of 216 hours of good data, the patient will be provided additional instruction and will be allowed to repeat the iPro proficiency test for an additional 2-week period. If the patient is unsuccessful after the second trial, he/she will be considered ineligible for the GLUMIT-DG study.

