## 1. Objectives

---

The principal objective of this multicenter, uncontrolled, open label treatment study is to assess the safety of RT-CGM as an adjunct to self monitoring blood glucose (SMBG) in guiding insulin pump therapy for 24 weeks by measuring mild, moderate, and severe hypoglycemic episodes in patients with type 1 or type 2 diabetes and gastroparesis.

Other objectives include:

- To determine the feasibility of achieving improved glycemic control with RT-CGM as an adjunct to SMBG-guided insulin pump therapy in patients with diabetes and gastroparesis.
  - To determine the efficacy of RT-CGM as an adjunct to SMBG-guided insulin pump therapy for 24 weeks as measured by improvements in symptoms of gastroparesis, gastroparesis-related quality of life, satiety, gastric myoelectrical activity, and autonomic function in diabetics with gastroparesis.
-

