**3.4 Standard treatment recommendations**

During the screening and run-in period that may span up to 16 weeks prior to enrollment into the GLUMIT-DG study, patients will receive a standardized set of recommendations to manage their gastroparesis symptoms including dietary modification, weight loss if needed, and exercise. In addition to dietary modification, patients may use antiemetic, prokinetic, or pain medications as appropriate for their gastroparesis symptom management. These recommendations have been prepared by the GpCRC

---

Steering Committee as standard of care in the management of patients with diabetic gastroparesis (see Standard Operating Procedures IV: Standard of Care for Patients with Diabetic Gastroparesis). This will help ensure that patients receive standard of care treatment for gastroparesis.

---

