### 4.2 Inclusion criteria

Patients with mild to moderate symptoms of diabetic gastroparesis will be studied. Patients should not have idiopathic or post-surgical gastroparesis etiologies and must satisfy the following inclusion criteria:

1. Age 18 – 70 years old at registration
2. Type 1 or type 2 diabetes mellitus for at least 2 years
3. Symptoms of gastroparesis (nausea, vomiting, early satiety, bloating fullness, discomfort) for at least 1 year prior to registration with a Gastroparesis Cardinal Symptom Index (GCSI) score of  $\geq 18$
4. Delayed gastric emptying on gastric emptying scintigraphy within 1 year of registration, defined as greater than 60% retention at 2 hours or greater than 10% retention at 4 hours
5. Hemoglobin A1c of at least 8.0% at registration with current therapy (insulin and/or oral hypoglycemic agents). This level of HbA1c indicates the need to advance treatment and makes the patient a candidate for insulin treatment (for those using oral agents only) or optimization of insulin therapy. Individuals already receiving diabetes therapy via an insulin pump will be eligible for participation if, in the opinion of investigators, he/she may acquire additional benefit from RT-CGM that might improve glycemic control
6. Normal upper endoscopy within 1 year of registration
7. No clinical or imaging evidence of obstruction
8. Successful use of the RT-CGM during the screening period
9. Access to a computer running Windows and with internet capabilities

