### 5.8 Standardized questionnaires

Two standardized questionnaires will be administered to patients enrolled in the GLUMIT-DG study. Questionnaires will be administered at baseline (prior to enrollment) and during follow-up at specified intervals (see Appendix 10.2 for the data collection schedule). The purpose of the questionnaires is to obtain important information regarding gastroparesis symptoms and health-related quality of life.

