| iPro CGM training                                               | X                                      | . | .                                          | . | .  | .  | .  | .  |
| Insulin pump training w/ RT-CGM                                 | .                                      | X | .                                          | . | .  | .  | .  | .  |
| Adverse event monitoring                                        | X                                      | X | X                                          | X | X  | X  | X  | X  |
| CBC, metabolic panel                                            | X                                      | . | .                                          | . | X  | .  | .  | X  |
| HbA1c†                                                          | .                                      | X | .                                          | . | .  | .  | .  | .  |
| Thyroid stimulating hormone                                     | X                                      | . | .                                          | . | .  | .  | .  | .  |
| Plasma banking                                                  | X                                      | . | .                                          | . | X  | .  | .  | X  |

**\*Run-in:** Four visits include training with the insulin pump and RT-CGMS to establish the baseline parameters.

**†Hemoglobin A1c (HbA1c):** Blood draw for HbA1c only will occur at the end of the run-in period

**Physical exam** includes measurement of weight, vital signs (temperature, heart rate, blood pressure), general physical findings

**Complete blood count (CBC):** white blood cells, red blood cells, hemoglobin, hematocrit, platelets

**Metabolic panel :** sodium, potassium, chloride, carbon dioxide, glucose, ketonemia, calcium, blood urea nitrogen (BUN) creatinine, albumin, total protein, alanine aminotransferase (ALT), aspartate aminotransferase (AST), bilirubin

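### The single pre-treatment symptom score appears both to decide entry (GCSI of at least 18) and to serve as baseline, which biases the uncontrolled GCSI change toward improvement

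*Protocol*

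**What the plan says.** Symptoms and quality of life are a stated efficacy objective. Protocol section 1 wants efficacy "as measured by improvements in symptoms of gastroparesis, gastroparesis-related quality of life, satiety" and further measures. Section 8.1 attributes the expected improvement to insulin pump treatment, and section 8.2 lists GCSI, PAGI-SYM and PAGI-QOL at baseline, week 12 and week 24.

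- **When the baseline is taken.** Section 5.3 puts both questionnaires at screening visit 1: "Symptom Severity Index (PAGI-SYM) questionnaires will also be completed as well as the Baseline Medical History and Physical Examination forms". Section 5.2 describes that visit as follows: "The goal of the first screening visit is to obtain consent, register the prospective participant for GLUMIT-DG". The schedule in section 11.2 marks both instruments at S, week 12 and week 24, and leaves the run-in column empty.
- **What decides entry.** Section 4.2 requires symptoms "for at least 1 year prior to registration with a Gastroparesis Cardinal Symptom Index (GCSI) score of" 18 or more.
- **Which forms exist.** Section 5.8: "Two standardized questionnaires will be administered to patients enrolled in the GLUMIT-DG study". These are PAGI-SYM and PAGI-QOL. No GCSI form is scheduled, so the GCSI has to come from PAGI-SYM.
- **What happens next.** Section 3.4 covers the time from screening to enrollment, at most 16 weeks, and says: "patients will receive a standardized set of recommendations to manage their gastroparesis symptoms including dietary modification, weight loss if needed, and exercise". Antiemetic, prokinetic or pain drugs may be used as appropriate. Section 5.6 continues this management during follow-up.
- **Contrast.** HbA1c, also an entry criterion, is measured again before enrollment: "Blood draw for HbA1c only will occur at the end of the run-in period" (section 11.2).

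**The concern.** A noisy score that must exceed a threshold is, on average, too high in those who pass. Measured again, it falls without any treatment. If the same score is then used as baseline, that fall is counted as change on treatment. Any benefit of gastroparesis care begun after the score is taken adds in the same direction, and there is no control arm to subtract either.

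Section 8.3 says that the pilot will supply potential effect sizes to inform the design of a randomized trial. A baseline with a known direction of bias weakens the symptom results for that use. The primary outcome, hypoglycemic episodes, is not touched.

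**Working it through.** **The plan's own GCSI figure.** Section 8.3 plans a fall from 27 (SD 15) to 20 (SD 15) with N = 40, Type I error 0.05, a correlation described only as modest, and power above 99%. For a paired change, SD of change = 15 × √(2(1 − ρ)) and power = Φ(7 / (SD of change/√40) − 1.96), two-sided:

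- ρ = 0.4: SD 16.43, standard error 2.60, ratio 2.69, power 77%
- ρ = 0.6: SD 13.42, standard error 2.12, ratio 3.30, power 91%
- ρ = 0.8: SD 9.49, standard error 1.50, ratio 4.67, power 99.7%

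The stated power needs ρ of about 0.76 two-sided (0.72 one-sided), which is hard to call modest. The plan therefore fixes no usable GCSI correlation, and I carry a range. The 0.6 in section 8.3 belongs to hypoglycemic episodes, not to GCSI.

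**Regression to the mean with no treatment effect.** Assume scores are normal with underlying mean m and SD s, with entry at 18 or above. Let z = (18 − m)/s. The mean of those selected is m + s·φ(z)/(1 − Φ(z)), and the expected fall on re-measurement is (1 − ρ)·s·φ(z)/(1 − Φ(z)).

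*Reading A: the planned 27 is the mean of enrolled patients.* The underlying SD is not in the documents, so it is assumed to be 8, 10 or 12, and m is solved so that the selected mean is 27.

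| s | m | z | φ(z)/(1 − Φ(z)) | 27 − m | Fall, ρ = 0.6 | Fall, ρ = 0.8 |
|---|---|---|---|---|---|---|
| 8 | 23.79 | −0.724 | 0.307/0.765 = 0.401 | 3.21 | 1.28 | 0.64 |
| 10 | 20.60 | −0.260 | 0.386/0.603 = 0.640 | 6.40 | 2.56 | 1.28 |
| 12 | 16.35 | 0.137 | 0.395/0.445 = 0.887 | 10.65 | 4.26 | 2.13 |

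The range is 0.64 to 4.26 points, or 9% to 61% of the planned 7. The top row of that range (s = 12) needs an underlying mean of 16.35, below the cut, so that only about 45% of those measured would pass. That sits poorly with section 5.2, where patients are invited after appearing eligible on chart review.

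*Reading B: 27 ± 15 describes the unselected population.* Then z = −0.6 and the ratio is 0.333/0.726 = 0.459. The selected mean is 27 + 6.89 = 33.9, and the fall is 4.1, 2.8 or 1.4 points at ρ = 0.4, 0.6 or 0.8. An enrolled mean of 33.9 does not match the planned baseline of 27, so Reading A is the more natural one.

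**What it does to a test.** This is a simulation with underlying mean 22 and SD 10, scores rounded and held to an assumed range of 0 to 45, N = 40, and a two-sided paired t-test. The enrolled mean is 27.3, close to the plan's 27.

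- Screening score as baseline, no treatment effect: mean fall 2.1 points at ρ = 0.6 and 1.1 at ρ = 0.8. The chance of a significant fall is 35% and 19%.
- A second score that does not decide entry as baseline: mean fall about 0.0, and a chance of about 2.5%, which is nominal for one direction.
- Screening score as baseline plus an assumed 2-point benefit of newly started care, ρ = 0.6: mean fall 4.1 points, chance 86%. The 2 points are illustrative only.

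**The case against.** **Same measurement.** A reader might infer that the protocol expressly uses one form for entry and baseline. It does not: section 4.2 names neither form nor visit for the qualifying GCSI, and section 5.2 allows chart review beforehand. The link is a strong inference, because no other GCSI source is scheduled.

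**Timing.** Section 5.2 calls the division of screening procedures a guideline that centers may rearrange. This stands, but moving one questionnaire within screening still leaves one score for both purposes.

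**Prior care.** It is tempting to say that standard gastroparesis care begins only after the score. Sections 3.1 and 5.2 draw patients from consortium studies and investigators' clinics, and many may already be under such care. Section 3.4 says drugs may be used, not that they start then. The care component could be small, but regression to the mean remains.

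**Size.** One might read the effect as 20% to 60% of the planned change. That singles out a correlation of 0.6, which has no special standing for GCSI, and its top end needs the implausible case above.

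**Disclosure.** Section 8.3 already says that a controlled study is needed for evidence of efficacy. That is fair and limits the weight of this point. It does not cover this part of the bias, which a second pre-treatment score reduces without a control arm. That a later trial would be undersized does not follow either: nothing says its designers would take the uncorrected change as the difference between arms.

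**Conclusion.** The point holds as a cheap improvement to a secondary outcome. One pre-treatment score, an entry cut on the same scale, and gastroparesis recommendations during the weeks that follow together bias the GCSI and PAGI-SYM change toward improvement. The direction of the regression part follows for any correlation below 1, provided that the qualifying score is the baseline score.

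Under the assumptions of Reading A (normal scores, enrolled mean 27, underlying SD 8 to 12, correlation 0.6 to 0.8), regression alone is roughly 0.6 to 4.3 points of the planned 7, with the upper end less plausible. Any benefit of newly started care is extra and cannot be sized from the documents.

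A reader might go further and conclude that the whole planned improvement would appear with no effect of glucose control, or that quality of life is biased to the same degree. Neither is supported. Regression alone falls short of 7 points throughout this range, and PAGI-QOL has no entry threshold, so it is affected only through its correlation with the GCSI.

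**What to change.** - Keep the screening PAGI-SYM for eligibility only.
- Repeat PAGI-SYM and PAGI-QOL at the start of run-in visit 1. Section 5.4 introduces RT-CGM at that visit and pump insulin at run-in visit 3, so the repeat precedes both. The end-of-run-in point used for HbA1c would be too late.
- State in section 8.2 that this second score is the baseline for all symptom and quality-of-life changes.
- Mark both instruments under R in section 11.2.
- Report the change from S to R as pre-treatment drift, which is itself useful for planning the randomized trial.

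The cost is a few minutes of patient time at an existing visit and an edit to the schedule. The symptom effect will probably be smaller. The symptom baseline would be dated later than the EGG, satiety and autonomic baselines, which stay at screening. Effects of gastroparesis care that arise during follow-up (section 5.6) would remain in the estimate.
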